#### 2.7.2. The Secondary Outcomes

The following outcomes will be the secondary effects that we will measure as part of our intervention:Well-being is “a state of complete physical, mental and social well-being, and not simply as the absence of disease”. This result will be measured through the WHO-5 Index [30] and the EQ-5D-5L questionnaire [31].Self-efficacy is the set of beliefs we have about our ability to complete a certain task. This result will be measured through the short version of the GSE self-efficacy scale [32].

### 2.8. Data Collection

In line with the design of the study, three different data collection tools were developed.

As reported in Table 2, the data collection sheet for primary users consists of four dimensions sections, which include a series of scales, as follows:(A)Health and Wellness Condition:Mini-Mental State Examination (MMSE) [33] is a neuropsychological test for the evaluation of disorders of intellectual efficiency and the presence of cognitive impairment. The test consists of 30 questions, which refer to various cognitive areas: orientation in time and space, recording of words, attention and calculation, re-enactment, language, and constructive praxis. The total score is between a minimum of 0 and a maximum of 30 points. A score of 26 to 30 is an indication of cognitive normality. The score is adjusted with the coefficient for age and schooling [34].Functional Ambulation Category (FAC) [35] is a scale that evaluates the ability to achieve autonomy in walking. The ambulatory capacity is evaluated with a score ranging from 0 to 5, where 0 indicates total dependence and 5 indicates complete independence. From the score obtained, it can be deduced the amount of support that the patient requires when walking and on what kind of surfaces he is able to walk.The Barthel Index [36] is an objective and standardized tool for measuring functional status. The individual is scored in a number of areas depending upon the independence of performance. Total scores range from 0 (complete dependence) to 100 (complete independence).SF-12v2 ™ Health Survey [37] is a widely used instrument and is a 12-element subset of the SF-36v2 ™. It is a short and reliable measure of the general state of health. It is useful in health surveys of large populations and has been widely used as a screening tool.Five Well-Being (WHO-5) Index [30] is a short self-reported measure of current mental well-being.EuroQol-5 Dimension-5 Level (EQ-5D-5L) [31] is a self-report survey that measures the quality of life across 5 domains: mobility, self-care, usual activities, pain/discomfort, and anxiety/depression. Each dimension is scored on a 5-level severity ranking that ranges from ‘No problems’ through ‘Extreme problems’.
(B)Self-efficacy:General Self-Efficacy Scale (GSE) [32]. Its abbreviated form of ten entries is a reliable and valid tool for assessing general self-efficacy.
(C)Usability and Acceptance:
System Usability Scale (SUS) [28] is a reliable tool for measuring usability. It consists of a 10-item questionnaire with five response options for respondents from ‘Strongly agree’ to ‘Strongly disagree’. It allows for evaluating various products and services, including hardware, software, mobile devices, websites, and applications. It is easy to administer to participants, can be used on small sample sizes with reliable results, and can effectively differentiate between usable and unusable systems.User Experience Questionnaire (UEQ-S) [29]. This short version of the questionnaire measures the subjective impression of users towards the user experience of products. The UEQ is a semantic differential with 26 items. Both classical usability aspects (efficiency, perspicuity, dependability) and user experience aspects (originality, stimulation) are measured.Quebec User Evaluation of Satisfaction with assistive Technology (QUEST—Version 2.0) [38] is a 12-item outcome measure that assesses user satisfaction with two components, Device and Services.
(D)Privacy and Stigmatization
Open questions

The data collection sheet for secondary users consists of a sequence of 5-Likert scale questions on the following dimensions (Table 2):Usefulness of the system,Reliability of the system,

and some free comments about satisfaction with the system.

The data collection sheet for tertiary users consists of a sequence of 5-Likert scale questions on the following dimensions (Table 2):Impact of the system on the reduction in time spent in caregiving activities;Impact of the system on the reduction in the cost of caregiving activities;Impact of the system on the reduction in the workload.

Each instrument will be administered, if possible, in a face-to-face session in the presence, otherwise remotely, of a trained interviewer, who will report the answers on a paper version of the data collection card.

During use, the following log data will be continuously recorded: usage time/used services (time/number), number of interactions, participation in social events (web conference, phone call, video call), tracked daily activities, number of errors, number of aids required for the tasks, recognized user commands, used input modality, captured touch screen data/activity, number of services used in the given period, number of tasks solved by using the SAVE system (for example, did the user recieve an answer to a question, did the user manage to call/inform the caregiver, was the user able to perform recreational activities with the help of the device, did the user manage to send the alarm to the caregiver, whether the caregiver was informed about the user’s fell, could not sleep, decreased activity, be deteriorated, etc.).

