## 2. Methodology

### 2.1. Study Design

To thoroughly evaluate the SAVE prototype, a pre-post interventional study involving the use of the SAVE platform for 21 consecutive days was designed. It consists of the use of a mixed-methods approach, in which it collects both qualitative (open questions) and quantitative (standardized tests) data in three different measurements (T0, T1, T2) during the period of use of the system. The data collection card will therefore be divided into three different sections, which correspond to the three different moments of detection:Prior to the start of the experimentation (T0);Ten days into the intervention study, i.e., at the midterm of the trial (T1);After 21 days, i.e., at the end of the trial (T2).

The users’ data will be logged and continuously stored over the 21-day test period. The research will be managed by qualified personnel, and the researchers will supervise the tests and the interactions between the users and the system.

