## 5. Conclusions

The SAVE system was developed using environmental sensors, smartwatches, smartphones, and a Web application to organize and provide improved service levels to older people, their caregivers, and care organizers. The main functions of the SAVE technology are fall detection, activity level monitoring, heart rate monitoring, door opening detection, water leakage detection, localization, enhanced touch and vocal communication, text messaging, and emergency calls. Data are stored in a cloud-based system that is securely accessible to older care recipients, their caregivers, and care managers.

The cross-national study was designed to evaluate the acceptance, usability, and efficiency of the SAVE system among 165 users of the three types. The exclusion and inclusion criteria for each user type were defined. The planned test environment is the elderly user’s home and the caregivers’ and care organizers’ Web platforms through their applications. The convenient user recruiting method will be applied with the help of retirement clubs and referrals through contacts. Training on using smart devices takes place during the first face-to-face meeting at system installation. The task of the older adult is to wear the watch during the day, put it on the charger at night, and test the alarm and message-receiving functions. Caregivers and care organizers are responsible for reacting to any dispatched notification and regularly opening the SAVE interface, reviewing the information on the interface, and using the information found as possible. The use of a control group is not planned.

The study design follows the mixed method approach where standardized tests and questionnaires, open-ended questions, and log data are collected from the users and the cloud database. The described study design could serve as an inspiring study design framework for similar usability and effectiveness studies.

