	Self-efficacy	GSE	X	X	X
	Usability and Acceptance	SUS		X	X
		UEQ-S		X	X
		QUEST 2.0		X	X
	Privacy and Stigma	Open questions	X	X	X
Secondary users	Usefulness		X	X	X
	Reliability		X	X	X
Tertiary users	Reduction in time		X	X	X
	Reduction in cost		X	X	X
	Reduction in workload		X	X	X

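### Table 2 has caregivers and decision-makers rate the system at T0, before any use, so any T0-to-T2 change in those ratings would mix expectation with experience

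*Protocol article*

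**What the plan says.** Section 2.1 describes "a pre-post interventional study involving the use of the SAVE platform for 21 consecutive days was designed". It sets the first measurement as "Prior to the start of the experimentation (T0") and the last as "After 21 days, i.e., at the end of the trial (T2"). The Conclusions add: "The use of a control group is not planned".

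Section 2.8 gives the content for the two non-patient groups:

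- **Secondary users (caregivers):** "The data collection sheet for secondary users consists of a sequence of 5-Likert scale questions on the following dimensions", namely usefulness and reliability of the system.
- **Tertiary users (care organisers and decision-makers):** Likert questions on the "Impact of the system on the reduction in time spent in caregiving activities", the "Impact of the system on the reduction in the cost of caregiving activities", and the corresponding impact on workload.

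Table 2 shortens the tertiary labels (for example "Reduction in time") and marks T0, T1 and T2 for all five dimensions. For primary users it marks only T1 and T2 for SUS, UEQ-S and QUEST 2.0.

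**The concern.** All five dimensions describe a property or an effect of the SAVE system. Before the experimentation starts, caregivers have had no use on which to judge reliability, and the system has had no effect on anyone's time, cost or workload. Whatever is answered at T0 is a forecast.

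The tertiary items raise a second difficulty. They already ask about a reduction, so T2 minus T0 is not a reduction in hours, cost or workload. It is the difference between a rated reduction and a hoped-for one.

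In an uncontrolled pre-post study, T0 is what a reader would take as the baseline. If it is used that way here, a system that helps exactly as much as people hoped shows zero change, and one that helps somewhat less shows a decline. At stake is the evaluation by caregivers and decision-makers, for whom these five dimensions are the only structured ratings listed.

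**Working it through.** **Step 1. Compare the schedule with itself.**

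| Respondent | What is rated | T0 | T1 | T2 |
|---|---|---|---|---|
| Primary | SUS, UEQ-S, QUEST 2.0 (the system) | – | X | X |
| Secondary | Usefulness, reliability (the system) | X | X | X |
| Tertiary | Impact on time, cost, workload (the system) | X | X | X |

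The table applies a rate-after-use rule to older adults and not to the other two groups. Section 2.6 confirms that caregivers lack access beforehand: their web accounts are created and linked in the last two set-up steps. The article mentions no separate expectation version of the T0 items.

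**Step 2. Reproduce the plan's own figure.** Section 2.9 states at least 34 end users per group from a dependent t-test (alpha 0.05, beta 0.2, effect size 0.5). Exact two-sided paired-t power at n = 34 uses noncentrality 0.5 × √34 = 2.915 on 33 degrees of freedom and gives 0.808; n = 33 gives 0.795. The 34 is reproduced. It does not bear on the timing question.

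**Step 3. How a pre-post contrast would behave.** None of the following means, SDs or correlations is in the documents.

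- Scale 1 to 5, neutral 3; SD 1 at each time; T0–T2 correlation r of 0 or 0.5.
- T2 mean 3.5, a favourable rating.
- T0 expectation E of 3.0, 3.5, 4.0 or 4.5.
- n = 80 secondary users (30 + 25 + 25, section 2.3).
- n = 15 tertiary users (at least 5 per site, taking three sites).

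Formulas: change = 3.5 − E; SD of the difference = √(2(1 − r)), which is 1.414 at r = 0 and 1 at r = 0.5; d = change / SD of the difference. The probability of a significant decline is the lower-tail rejection probability of the two-sided 5% paired t-test, from the noncentral t with n − 1 degrees of freedom and noncentrality d√n.

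Example with E = 4.0 and n = 80: change −0.5. At r = 0, d = −0.354, noncentrality −3.16, probability 0.878. At r = 0.5, d = −0.5, noncentrality −4.47, probability 0.993.

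| T0 expectation | Mean change | Significant decline, n = 80 | Significant decline, n = 15 |
|---|---|---|---|
| 3.0 | +0.5 | about 0% | 0.1% or less |
| 3.5 | 0 | 2.5% | 2.5% |
| 4.0 | −0.5 | 88% to 99% | 25% to 44% |
| 4.5 | −1.0 | about 100% | 72% to 95% |

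The T2 rating is the same favourable 3.5 in every row. Only the prior expectation differs, and the change runs from +0.5 to −1.0.

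**Step 4. Sensitivity to the tertiary count.** The stated total of 165 leaves 165 − 80 − 80 = 5 tertiary users, not 15. With n = 5 and E = 4.0 the probability of a significant decline is 9% (r = 0) to 14% (r = 0.5). The sign of the expected change is unaffected.

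**The case against.** The strongest reply is that the harmful analysis is inferred. Section 2.9 names the dependent t-test only for sample size, does not tie it to caregiver or decision-maker items, and defers to an analysis plan that is not shown. That stands: a reader might infer that the article plans a T0-to-T2 test of these ratings, and it does not say so.

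The questions themselves are not printed, only dimension labels. Section 2.1 says the data collection card has a separate section for each time point, so the T0 questions could be worded as expectations. That also stands. But a T0-to-T2 difference would then still compare two different things, and labelling them is what is asked for. Likewise, a reader might infer that users must report reductions already achieved at T0. The text speaks of impact on a reduction, which could be asked prospectively.

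A further tempting reading is that the sign of the change reflects optimism alone and not the system. It depends on both: T2 experience enters the difference as much as T0 expectation does, and low expectations would produce a rise.

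Finally, none of the five dimensions is a primary or secondary outcome in section 2.7, and valid post-use ratings are collected at T1 and T2 whatever is done with T0. Both are true and limit the consequence. They do not remove the inconsistency in Table 2, which is a fixed schedule and not a detail left to an analysis plan.

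**Conclusion.** The point holds in a limited form. Table 2 fixes a pre-use measurement for five ratings that can have no experiential content before use, against the rule the table itself follows for SUS, UEQ-S and QUEST 2.0. If T0 serves as the baseline for these items, the change combines prior expectation with experience, and a favourable T2 rating may appear as no change or a decline. Under the assumptions above, an expectation half a point above experience would be enough to produce a significant decline in 80 caregivers with probability 88% to 99%.

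This rests on assumed means, SDs and correlations, and on the pre-post logic being extended to these items. It is possible, not certain. The SUS, UEQ-S, WHO-5, EQ-5D-5L and GSE results are untouched, and no sample-size figure changes.

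**What to change.** In Table 2, either remove the T0 mark for the five secondary- and tertiary-user dimensions or add a footnote stating that T0 records expectation. Exclude T0 from any pre-post effect test on these items. Report the T1 and T2 levels as the result: the response distribution, the mean and its 95% CI. If T0 answers are kept, show T2 minus T0 only as a gap between expectation and experience, under that name.

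Do not change the T0 questions at some sites only. Section 2.5 says data collection began in September 2022, and the Discussion requires the same conduct in all countries; a partial change would mix instruments.

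The cost is a footnote and a sentence of analysis wording, which can also be applied to data already collected. The downside is that there will be no pre-post effect estimate for caregivers and decision-makers.

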### 2.9. Data Analysis

The proposed study is a small-scale study, carried out as part of an innovation and research project. To calculate sample size, G*Power software (latest ver. 3.1.9.7; Heinrich-Heine-Universität Düsseldorf, Düsseldorf, Germany) [39] was used. The G*Power software supports sample size and power calculation for various statistical methods, including dependent t-test (differences between two dependents means—matched pairs). A power calculation based on a dependent t-test shows that at least 34 end users per group are needed (alpha set at 0.05, beta 0.2 and effect size at 0.5 medium). It will conduct only a partial evaluation of the effectiveness of the services to specific dimensions of the quality of life of the subjects involved. To investigate primary and secondary objectives, the data will be analyzed using qualitative and quantitative methods and mixed analysis methods.

The processing of questionnaire data will be performed through specific software, such as SPSS, Mplus (for the execution of the confirmatory factor analysis), and AMOS (for the execution of the exploratory factor analysis), depending on the needs. The quality of the data and its internal consistency will be evaluated using the Cronbach Alpha and other specific tests. The questionnaires will first be verified manually to check the completeness of the compilation and any apparent inconsistencies. Later, automated routines will be used to detect dubious outliers and records. In such cases, the necessary data cleaning will be carried out.

An Analysis Plan will be defined on the basis of which the analyses themselves will then be conducted. The first step of the analysis will be exploratory in nature. The descriptive analysis of the sample will be conducted through the classic techniques of uni- and bi-variate statistical analysis. Significant differences between outcomes and exposures will be compared using the Chi Quadro test, the Fisher Exact, the t-test, or the Anova test. The characteristics of the subjects will be compared with those of the non-respondents to verify any distortions due to non-responses during the detection.

## 3. Discussion

In this study, we have described a feasibility protocol to evaluate the usability and acceptability of the SAVE system for enabling older adults to keep their independent and active lives in their homes and to maintain their social relationships for as long as possible. This is closely related to the concept of “aging in place”, which represents the desire expressed by older people to continue living within the community, with some level of independence, rather than in residential care [40]. Housing and neighborhood satisfaction have been used as good indicators of environmental and overall well-being for older adults [41]. Technological devices should provide a sense of confidence and security for older adults, which would enable aging in place. In that sense, the SAVE intervention has the potential to assist older people to live in their own homes and facilitate their engagement in everyday tasks, helping to maintain their independence and increasing their control over the world around them. Several studies [42,43,44,45,46,47] have claimed that older people want to remain independent for as long as possible. The desire to stay independent stemmed from their wish to not be perceived as a burden to family, friends, or society. Therefore, the smart home solutions would be designed to help older people carry out everyday activities and lead healthier and more fulfilled lives by improving their physical safety and social communication. According to Lee and Kim [48], older adults’ active participation in social activities and establishing their sense of belonging as social members have important effects on successful aging in place. The SAVE system would effectively overcome social isolation among older people by connecting to the outside world, gaining social support, engaging in activities of interest, and boosting self-confidence.

The study must be performed the same way in all participating countries to obtain comparable data from the three countries. However, there are also limitations in the applicability of the intervention. According to Quan-Haase et al. [49], age-related factors beyond income, education, and gender affect older adults, hindering their ability to take advantage of digital technology. Low digital literacy could hinder older people’s use of digital media, perhaps because they did not grow up with it and had to learn and adapt in order to use them later in life [50]. A limited number of participants with a specific level of cognitive impairment is also a limitation, as well as the fact that the recruitment of the subjects and the beginning of the trial will take place when the COVID-19 pandemic is still an ongoing threat. Despite this, in emergency situations, technology has proved to greatly help in mitigating the consequences of physical distancing and helping older people maintain relationships with their relatives and friends [51].

## 4. Ethics and Dissemination

The study was approved by the Ethical Committees of the three countries involved. Any protocol modifications will be notified to the same Ethics Committees and to other interested parties, such as researchers and participants. For the latter, changes will be communicated by email. The principles of the Declaration of Helsinki and Good Clinical Practice guidelines will be adhered to. Participants in this study will provide written informed consent.

### 4.1. Risk Management, Mitigation, and Possible Limitations for the Users

We do not expect any adverse effects on users’ health related to testing the technology platform. The hardware devices used are commercial devices (Samsung smartwatches and AQARA-XIAOMI environmental sensors) and CE-certified. Researchers will provide clear and detailed information on the terms of use of the technology platform and the services offered during the study. The proposed services aim to support older people in terms of personal and residential security by allowing them an independent and safe lifestyle, even when the first signs of disorientation could lead the individual and their family members to progressive isolation and social exclusion, and do not replace (in whole or in part) the support from professional services, as the proposed technologies support the well-being of the participants.

The users who take part in the study will not incur any direct or indirect costs related to the use of the technology platform. All the devices necessary for the trial (smartwatches, smartphones, sensor kits and internet connection) will be made available to users free of charge.

Even if we do not expect any adverse effects, the presence and use of technological devices (sensors and smartwatches) could be a source of discomfort, anxiety about making mistakes, or quickly forgetting the instructions and feeling stigma. Low digital literacy and the poor usability of the devices could hinder older people’s use of technologies. The SAVE technology has been designed and developed according to the UCD approach to counteract these possible limitations by matching the needs and capabilities of users, thereby improving the user experience [27]. The pre-post interventional study design will allow us to better analyze changing behaviors regarding usability, acceptance, and stigma.

The use of a specific manufacturer’s company (Galaxy Gear app) probably significantly limits the range of users, but the operating systems for smartwatches are still very fragmented, and the budget resources of the project are limited. Therefore, for our research, we chose a product of a large company with a significant market share. We aimed for a product with LTE connectivity (based on eSIM), which makes it independent of a smartphone and allows a better monitoring process. At the time of selection, there were not many products with LTE connectivity, and the eSIM technology was not yet supported by all service providers for all smartwatch producers. The architecture we adopted lends itself to the easy inclusion of other devices from other manufacturers by adding a software element (an adapter), which is in our expansion plans.

